**Discussion:**

The results of this comparative anaesthesiological trial should whether each the three hypnotics tested is related to a significantly different postoperative delirium rate. This information could ultimately allow us to select the most appropriate hypnotic to maintain anaesthesia for specific subgroups of patients and especially for those at high risk of postoperative delirium.

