### Inclusion and exclusion criteria

Inclusion criteria are age > 18 and < 75 years; American Society of Anesthesiology (ASA) I-III; with no neurological deficits and Glasgow Coma Scale (GCS) Score of 15 [21,22].

Exclusion criteria: Patients with a history of drug abuse, preoperatively foreseen delayed extubation; any condition preventing proper evaluation of cognitive functions such as speech and sensory impairment or psychiatric disorders (language difficulties or psychiatric organic dysfunctions) that could make difficult to administer psychometric tests, will not be enrolled in this study.

To minimize the influence of surgical procedures on postoperative neurocognitive status, patients undergoing cardiac or brain surgery will be excluded. To reduce the risk of PD, premedication benzodiazepine or atropine will be avoided, because the use of these drugs is associated, especially in patients at higher risk, to an excess of PD incidence [23,24]. Premedication could be accomplished with fentanyl (up to 1 mcg/kg) or propofol (up to 0.5 mg/kg). All patients will receive isotonic crystalloid saline solution (5 mL/kg) before anaesthesia induction to minimize the risk of arterial hypotension after anaesthesia induction and will be preoxygenated for 3 minutes with a reservoir bag in 100% O_2 _before intubation to prevent hypoxia. After anaesthesia induction a second intravenous line will be placed for study drug administration purposes. In all patients, anaesthesia will be induced with propofol (2-3 mg/kg IV), fentanyl (2 to 4 μg/kg IV) and non-depolarizing neuromuscular blocking drugs.

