After tracheal intubation, patients will be mechanically ventilated with an inspired mixture of air and oxygen (1:1). Ventilation, using a semi-closed breathing system with a fresh gas flow of at least 2 L/min during anaesthesia maintenance, will be adjusted to achieve end-tidal carbon dioxide varying from 30-35 mmHg. No local anaesthesia will be allowed. Anaesthesia will be maintained according to one of the following three study groups: *desflurane + fentanyl*: desflurane will be maintained in a 5.6 to 6.1 MAC intervals and fentanyl (2-3 μg/kg/**h **or 0.7 μg/kg boluses). If necessary, fentanyl (1-2 μg/kg/**h**) can be supplemented just before skin incision; sevoflurane + fentanyl: sevoflurane will be maintained in a 0.75 to 1.25 MAC interval and fentanyl (2-3 μg/kg/**h **or 0.7 μg/kg boluses). If necessary, fentanyl (1-2 μg/kg/**h**) can be supplemented just before skin incision; *propofol + fentanyl*: propofol will be maintained with continuous infusion at 10 mg/kg/h for the first 10 minutes, then reduced to 8 mg/kg/h for the ensuing 10 minutes and reduced to 6 mg/kg/h thereafter. If necessary, fentanyl (1-2 μg/kg/**h**) can be supplemented just before skin incision.

The administration of the assigned hypnotic (desflurane, sevoflurane or propofol) will be stopped at skin dressing. During awakening phase fresh gas flow will be increased to the "minute volume" of the individual patient. When surgery ends, residual neuromuscular blockade will be antagonized with neostigmine 2.5 mg and atropine 1 mg or glycopirrolate at 25% recovery of the first train of four (TOF)-induced twitch and patients were allowed to recover to a TOF ratio of 0.9. Administration of paracetamol (1 g IV) for postoperative analgesia, will be started at surgical wound closure and continued at the dose of 1 g 3 times/day, if necessary opioids can be used to supplement postoperative analgesia.

Postoperative (post-anesthesia) pain will be evaluated every 20 minutes, once patients reach a postoperative Aldrete score ≥ 9, for the first postoperative hour (20, 40, and 60 min) [25]. Research assistants, unaware of the group assignment, will record postoperative pain scores reported by patients during structured interviews using a verbal version of the Visual Analog Scale (VAS), in which a rating of zero corresponds to no pain, ratings of 1-4 indicate moderate pain, and ratings of 5-10 correspond to severe pain [26].

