Postoperative (post-anesthesia) cognitive function will be evaluated with 2 test batteries administered individually to all patients at 4 times: before surgery (baseline), and postoperatively-after patients reach a postoperative Aldrete score ≥ 9-every 20 minutes for the first postoperative hour (20, 40, and 60 min). The Short Orientation Memory Concentration Test (SOMCT) is a patient-based test designed to assess cognitive function in terms of level of orientation, memory, and concentration. The SOMCT requires subjects to recall the current year, month, time, a complete sentence, and to repeat in numerical and reverse order the sequence of the months of the year. These 6 variables yield scores varying from 0 to 28, with higher scores indicating better cognitive function [27,28] (Appendix 1, Table 1). The Rancho Los Amigos Scale is a physician-based scale designed to quantify behavioural and cognitive status after acute brain injuries also used in the postoperative intensive care setting. Each state corresponds to 1 of 8 levels, varying from I to VIII, with higher levels indicating better behavioural and cognitive status (Appendix 2, Table 2). Both scales will be evaluated preoperatively and postoperatively by 2 experienced physicians unaware of the group assignment. If the 2 observers' score disagree, the opinion of a third observer will be considered discriminant. The Aldrete score will be assessed by a trained anaesthesiologist, blinded to the allocation treatment group [26]. Every 30-60 seconds the anaesthesiologist will score the patients' activity (ability to move extremities), respiration (ability to cough and breath), circulation (differences in blood pressure from patient's personal baseline), consciousness (ability to keep awake) and skin color (level of peripheral oxygen saturation).

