The incidence of postoperative delirium will be evaluated using the Nursing Delirium Scale (Nu-Desc) a tool that can be easily integrated into routine care and clinical practice. The Nu-Desc is a five-item scale that comprises a fifth item for the rating of unusual psychomotor retardation. This scale also takes into account the subjects medical condition (delayed responsiveness, few or no spontaneous actions or words; for example, when the patient is prodded, the reaction is deferred or the patient is unarousable). A positive response to these items brings the maximal screening score to 10. A score of 2 or more on the Nu-Desc correctly identifies the presence of delirium [29,30] (Appendix 3, Table 3). The onset of postoperative delirium will be monitored with the Nu-DeSc every three hours up to 72 hours post anaesthesia.

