## Discussion

The results of this multicentre, double-blind, prospective, randomized, controlled clinical trial will help anaesthesiologists to be able to choose the hypnotic drug least likely to induce PD after general anaesthesia for surgical procedures other than cardiac or brain surgery. By clarifying the influence of PD on early postoperative cognitive impairment our findings should also help tailor hypnotic-anaesthesiological strategies to the individual patient. The subgroup analysis used to categorize patients according to demographic variables relevant to the risk of PD (age, sex, body weight) and to the preoperative score index for delirium, should help to defined the risks of PD in the various subgroups.

We sought that excluding patients undergoing surgical procedures other than cardiac or brain surgery will minimize the influence of hemodynamic variablitiy and the surgical procedure per se on the postoperative neurocognitive status of the patients. The risk of PD can be predicted and effective strategies exist to reduce this risk. In 126 patients undergoing hip fracture repair to receive usual care alone or supplemented by several additional measures (including: supplemental oxygen during surgery, optimizing electrolytes and blood glucose preoperatively, discontinuing high-risk medications, maintaining adequate nutritional intake, encouraging patients to get out of bed on the first postoperative day, treating severe pain), reduce delirium rate from 50% to 32% in the intervention group and severe delirium rate from 29% to 12% [34].

Several drugs can increase the risk of PD and worsen postoperative cognitive recovery. Perioperative atropine and other drugs with anticholinergic properties, ie, benzodiazepines and the opioid agent meperidine increase the risk of PD. In general, the older the patient, the less appropriate are these agents [24]. Many drugs not typically recognized as anticholinergics, including tricyclic antidepressants, first-generation antihistamines and high-dose H_2_-receptor blockers may have potent anticholinergic activity therefore these agents too should be avoided in elderly patients [35]. Postoperative impairment of memory and concentration has been attributed to benzodiazepines in elderly patients undergoing cataract surgery, with a statistically significant correlation between the extent of impairment in the memory performance and amount of nitrazepam given during the postoperative week [36].

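### Atropine 1 mg is an equal option for reversing neuromuscular block, at odds with the protocol's own reasons for avoiding atropine

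*Protocol article*

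**What the plan says.** All statements come from the protocol article.

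- **Premedication** (Methods, Inclusion and exclusion criteria). The plan is that "premedication benzodiazepine or atropine will be avoided, because the use of these drugs is associated, especially in patients at higher risk". Both the stated aim and the harm named in that sentence concern PD.
- **Reversal** (same section). When surgery ends, "residual neuromuscular blockade will be antagonized with neostigmine 2.5 mg and atropine 1 mg or glycopirrolate". Atropine has a stated dose, and neither agent is preferred.
- **Outcome assessment** (same section). Cognitive tests are given at 20, 40 and 60 minutes in the first postoperative hour, once the Aldrete score is at least 9. For the primary outcome, "The onset of postoperative delirium will be monitored with the Nu-DeSc every three hours up to 72 hours post anaesthesia".
- **Discussion**. The paragraph on drugs opens with "Several drugs can increase the risk of PD and worsen postoperative cognitive recovery" and continues: "Perioperative atropine and other drugs with anticholinergic properties, ie, benzodiazepines and the opioid agent meperidine increase the risk of PD". It then adds that, in general, "the older the patient, the less appropriate are these agents".
- **Abstract, Discussion**. The results are meant to guide the choice of hypnotic for subgroups, "especially for those at high risk of postoperative delirium".

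**The concern.** The investigators take one step to keep atropine away from patients, and they give PD as the reason. At a later step, nearer to the outcome assessments, they allow 1 mg of the same drug as a free choice. Their Discussion does not confine the warning to premedication: it speaks of the perioperative period, which includes reversal at the end of surgery.

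Two things are at stake. Patients can receive a drug that the document itself says raises the primary outcome, although another permitted agent stands in the same sentence. Also, the choice of anticholinergic is left open in a trial that otherwise tries to hold background drugs constant; fentanyl, for example, is used in every arm in order to limit confounding.

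**Working it through.** The point rests on the text, so the check sets the statements side by side.

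1. **Does the premedication restriction reach reversal?** No. It names premedication only, so giving atropine with neostigmine does not breach it.
2. **Does the stated reason reach reversal?** Yes. The reason is an excess of PD with atropine, and the Discussion applies it to perioperative use. Reversal when surgery ends is perioperative.
3. **Who can be exposed?** Non-depolarizing blockers are part of induction in all patients, so the choice of agent can arise in any of them and in any arm.
4. **Is the timing relevant?** Reversal comes before every postoperative outcome assessment. There are steps in between: recovery to a train-of-four ratio of 0.9, then an Aldrete score of at least 9, then the tests. "Before" is accurate; "immediately before" would overstate it.
5. **Does the article name glycopyrrolate as a PD risk?** Not by name. But the Discussion also blames other drugs with anticholinergic properties, and nothing in the article exempts glycopyrrolate from that class.

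**The sample size is not touched.** Inputs (Sample Size section): reference rate 10%, true treatment rate 7%, margin 3 points, one-sided alpha 0.05, power 80%, Farrington-Manning score test.

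- Distance from the margin: 0.03 + (0.10 − 0.07) = 0.06.
- Restricted rates under the null: 0.10454 (treatment) and 0.07454 (reference), so s0 = √(0.10454 × 0.89546 + 0.07454 × 0.92546) = 0.4032.
- Under the alternative: s1 = √(0.07 × 0.93 + 0.10 × 0.90) = 0.3938.
- n = [(1.645 × 0.4032 + 0.842 × 0.3938) / 0.06]² = 274.9 with unrounded inputs, so 275 per group and 825 in total, as the plan states.

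Nothing in this calculation depends on the reversal agent. Any effect of added PD on power could go either way. A fixed number of extra points in every arm would leave the 0.06 distance unchanged and raise the variance. A proportional increase would widen the distance as well as raise the variance. The article supports neither model, so no power figure is given.

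**How many patients a change could still reach.** By the Results section, 269 were enrolled by April 2011. 825 − 269 = 556, and 556/825 = 67%. This is the number still to be enrolled, not the number who would receive atropine.

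**The case against.** The strongest reply is that this reflects a preference between drugs and is not a defect. Premedication is optional, whereas the article requires residual block to be antagonized and pairs an anticholinergic with neostigmine to do so. Avoiding an optional use while allowing the drug within reversal is a coherent position. **This stands to the extent that no rule is breached.** It does not explain why atropine is on an equal footing with an alternative that is already permitted, given a Discussion that names atropine across the whole perioperative period.

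The second reply is that the article does not show glycopyrrolate to be safer, since its warning extends to other anticholinergics. **This stands in full.** A reader might infer that changing the agent would lower the PD rate; the document does not support that.

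The third reply is that PD risk may be lower in this population. The Discussion grades its caution by age, and the trial enrols patients aged over 18 and under 75 without neurological deficits. **This stands too**, and it is one reason why the size of the benefit is unknown.

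Other stronger readings also fail:

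- *Bias between arms.* The reversal rule is written once for all three arms, and nothing in the article indicates that use differs by arm.
- *Harm falling mainly on high-risk patients.* The article says only that the association is seen especially in that group; it does not say where most of the excess lies.
- *A count of extra PD events.* Neither the effect of atropine nor its frequency of use is given, and any assumed share of users would count exposures rather than harm.

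Finally, an article may leave the reason for a drug choice, or the recording of the agent, to the full protocol. Their absence is not part of this point. The point is the conflict between statements that the article does make.

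**Conclusion.** The concern holds as a **minor** inconsistency that is cheap to remove. The reversal step offers atropine as an equal option, while the same document avoids atropine premedication to reduce PD and says that perioperative atropine increases PD. Followed as written, the plan can expose patients to a drug that it names as a risk for its own primary outcome.

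The conclusion assumes only that the article's statements about atropine are meant as written and that end-of-surgery reversal counts as perioperative. The gain from a change is consistency with the stated rationale, less exposure to a drug named as a PD risk, and a more uniform reversal regimen. The size of that gain cannot be derived from the document. The randomised comparison and the planned 275 per group are unaffected.

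**What to change.** For the remaining patients in all three arms, amend the reversal instruction so that glycopyrrolate, already allowed, is the default agent with neostigmine, at a dose the investigators set. Keep atropine for documented clinical need. If the investigators have a reason to keep both agents on an equal footing, they should set it against their own statements on atropine.

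Costs:

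- a short amendment;
- a glycopyrrolate dose to be fixed, since the article states none;
- less discretion for the anaesthetist;
- two periods of care, with 269 patients enrolled by April 2011 and at most 556 after the change. Because patients are randomised concurrently with equal probability and in blocks at each site, the change affects all arms alike and does not bias the comparison between them.

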#### Statistical Analysis

##### Sample Size

This trial has the objective to evaluate if propofol + fentanyl, as well as sevoflurane + fentanyl, is non inferior to desflurane + fentanyl, in terms of PD. To test for non inferiority two comparisons are planned:

✓ propofol + fentanyl vs. desflurane + fentanyl

✓ sevoflurane + fentanyl vs. desflurane + fentanyl

A sample size of 275 patients for each study group, with an allocation ratio of 1:1:1, for a total of 825 patients, is required to achieve 80% power -with a significance level of 0.05- to detect a non-inferiority margin difference between the group percentage of 3% in the primary end-point variable (PD rate). The reference group percentage is 10%. The treatment group percentage is assumed to be 13% under the null hypothesis of inferiority. The power was computed for the case when the actual treatment group percentage is 7%. Sample size calculation has not been corrected for possible multiple comparisons. The statistical test used was the one-sided Score test (Farrington & Manning) [31]. Calculations were implemented in PASS2005 [32].

Patients will be randomly assigned in consecutive order in allocation blocks. No patient stratification will be done. Dunnett's test will be used after ANOVA to test the null hypothesis that no group has its mean significantly different from the mean of the reference group [33].

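### The 80% power belongs to uncorrected score tests, but the group analysis named is Dunnett after ANOVA, which adjusts for multiplicity and does not test the 3-point margin

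*Protocol article*

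**What the plan says.** Everything on this point stands in the Sample Size section of the protocol article, under Statistical Analysis.

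- **Objective.** Propofol and sevoflurane, each with fentanyl, are to be shown non-inferior to desflurane with fentanyl on postoperative delirium: "To test for non inferiority two comparisons are planned". Both use the same desflurane arm.
- **Size.** "A sample size of 275 patients for each study group, with an allocation ratio of 1:1:1, for a total of 825 patients". These numbers are set for a power of 80% at the 0.05 level. The margin is 3 percentage points, the reference rate 10%, the treatment rate 13% under the null, and 7% for the power calculation.
- **Test behind the size.** "The statistical test used was the one-sided Score test (Farrington & Manning"), run in a sample size package.
- **Multiplicity.** "Sample size calculation has not been corrected for possible multiple comparisons".
- **Analysis.** "Dunnett's test will be used after ANOVA", with a null hypothesis about group means against the mean of the reference group. The sentence names no endpoint and no margin.

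The section does not say whether 0.05 applies to each comparison or to the pair, or how the sizing test relates to the analysis test.

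**The concern.** The trial is sized on one criterion, and the analysis named in the same section uses another. They differ in two ways.

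First, Dunnett's test is a many-to-one procedure built to hold the error rate over all comparisons with the reference. Its cut-off is stricter than the 1.645 used to obtain 275. If it governs the primary comparisons, power is below 80%. If it does not, 5% is a per-comparison rate and the familywise rate is higher.

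Second, a null of equal means is not the null of the sample size calculation, which is that delirium is at least 3 points more frequent than with desflurane. Failing to find a difference in means does not show non-inferiority.

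The primary conclusion is at stake. A comparison with a test statistic between 1.645 and 1.916 succeeds under the sizing rule and fails under a one-sided Dunnett rule.

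**Working it through.** **Inputs (all from the Sample Size section).** Reference rate 0.10; true treatment rate 0.07; margin 0.03; 275 per arm; one-sided 0.05; two comparisons sharing one control arm.

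**1. Reproduce the stated 275.** The Farrington-Manning formula is n = [(c·s0 + z_power·s1)/d]².

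- Distance to the margin: d = 0.03 − (0.07 − 0.10) = 0.06.
- Restricted maximum-likelihood rates, with treatment minus reference held at 0.03: 0.1045 and 0.0745. So s0 = √(0.1045×0.8955 + 0.0745×0.9255) ≈ 0.4032.
- s1 = √(0.07×0.93 + 0.10×0.90) = √0.1551 ≈ 0.3938.
- With c = 1.645 and z_power = 0.842: n = [(0.6633 + 0.3315)/0.06]² ≈ 274.9, so 275.

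The stated figure is exact for an uncorrected one-sided 5% test of each comparison.

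**2. Familywise error without correction.** Take both drugs at the margin and correlation 0.5 from the shared arm. Then 1 − P(Z1 < 1.645, Z2 < 1.645) = 0.0878. With the correlation implied by rates of 13%, 13% and 10%, which is 0.09/(0.1131 + 0.09) = 0.44, it is 0.0894. If the two tests were independent it would be 1 − 0.95² = 0.0975.

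**3. Power under adjusted cut-offs.** The large-sample one-sided Dunnett cut-off solves P(Z1 < c, Z2 < c) = 0.95 at correlation 0.5. This gives c = 1.916, or one-sided 0.0277 per comparison. Power at 275 is Φ[(0.06×√275 − c·s0)/s1]. For Dunnett this is Φ[(0.9950 − 0.7727)/0.3938] = Φ(0.564) = 0.714.

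| Rule | Cut-off | Power per comparison at 275 | Per arm for 80% |
|---|---|---|---|
| Uncorrected, one-sided 5% | 1.645 | 80.0% | 275 |
| Dunnett, one-sided 5% familywise | 1.916 | 71.4% | 339 |
| Bonferroni, one-sided 2.5% each | 1.960 | 69.8% | 350 |
| Dunnett, two-sided 5% familywise | 2.212 | 60.3% | 416 |

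**4. Power for more than one claim.** With both drugs truly at 7%, the two test statistics have correlation 0.09/0.1551 = 0.58. Uncorrected, the chance that both succeed is 69.7% and that at least one succeeds is 90.3%. Under one-sided Dunnett, the chance that at least one succeeds is 84.1%.

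**5. Dunnett as worded.** A plain test of no difference, 10% against 7% at 275 per arm, has standard error under the null √(2×0.085×0.915/275) ≈ 0.0238. Its power is about 24% at two-sided 0.05 and about 17% with the two-sided Dunnett cut-off. These figures show how far that hypothesis is from the one that was sized.

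**The case against.** Four arguments on the other side have force.

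- **The stated pair is attainable, and the lack of correction is disclosed.** A reader might infer that 5% and 80% can never hold together, or that 275 is miscalculated. The documents do not support either. Under the score test named for sizing, each comparison has exactly 80.0% power at one-sided 5%. Testing two different drugs at 5% each is also a position that can be defended, particularly in a trial the Methods section calls phase II. This stands. What the disclosure does not do is reconcile the sizing with an analysis that does correct.
- **Dunnett may be meant for other outcomes.** The sentence speaks of means and names no endpoint. Pain and cognitive scores have means, and the Abstract speaks of odds ratios for delirium. This reading is possible. But the sentence sits with the sizing of the delirium comparisons, and it is the only group-comparison analysis the section gives. If it does concern the scores, the section's only margin-based test is the one named for the sample size calculation, and the same clarification is needed.
- **The harms cannot be added together.** If both claims are required, no correction is needed and the 8.8% does not apply. Pairing a Dunnett cut-off with a both-must-succeed rule gives about 59%, but that combines two rules that would not be used together, so it is not counted here. If the claims are separate, joint power is not the target. The article does not say which applies.
- **The statistical analysis plan may settle the rule.** A reader might infer that the choice of rule is open until the data are seen. The article does not show that, and the point does not rest on it. It rests on two statements in one section that do not fit together.

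**Conclusion.** The concern holds as a mismatch between design and analysis, not as an error in the arithmetic of 275. The stated 5% and 80% describe each comparison under an uncorrected score test, with familywise one-sided error of about 8.8%. They do not describe the multiplicity-adjusting analysis named in the same section. Under a one-sided Dunnett criterion at familywise 5%, power at 275 per arm is about 71% per comparison. If both claims are required, power is about 70% with no correction. In addition, the null of equal means attached to Dunnett's test does not address the 3-point margin at all.

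The figures assume the plan's own rates (7% in both treatment arms, 10% with desflurane), large-sample normal approximations, and correlation 0.5 for the Dunnett cut-off. The 71% applies that cut-off to the Farrington-Manning test, an analysis the article does not itself describe.

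**What to change.** Amend the statistics section in three respects.

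1. Name the Farrington-Manning non-inferiority test, or the matching confidence bound against the 3-point margin, as the primary analysis of the delirium rate, in place of ANOVA and Dunnett on means. If Dunnett is meant for the score outcomes, say so.
2. State whether 0.05 is per comparison or familywise.
3. Restate power to match one of two rules:
   - **Fixed order, each test at one-sided 5%.** Familywise error is held at 5%, the leading comparison keeps 80% power, and both claims have about 70%. The cost is that the other comparison can be claimed only if the leading one succeeds. The order must be chosen and stated, because listing propofol ahead of sevoflurane does not establish a hierarchy.
   - **Dunnett-adjusted non-inferiority bounds.** The two claims stand independently of order. The cost is a stated power of about 71% per comparison instead of 80%.

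Either rule needs a few sentences and no extra patients. Keeping 80% per comparison under one-sided Dunnett would instead take 339 per arm, or 1,017 in total against 825.

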**Methods/Design:**

After local ethics committee approval, enrolled patients will be randomly assigned to one of three treatment groups. In all patients anaesthesia will be induced with propofol and fentanyl, and maintained with the anaesthetics desflurane, or sevoflurane, or propofol and the analgesic opioid fentanyl.

The onset of postoperative delirium will be monitored with the Nursing Delirium Scale every three hours up to 72 hours post anaesthesia. Cognitive function will be evaluated with two cognitive test batteries (the Short Memory Orientation Memory Concentration Test and the Rancho Los Amigos Scale) preoperatively, at baseline, and postoperatively at 20, 40 and 60 min after extubation.

Statistical analysis will investigate differences in the hypnotics used to maintain anaesthesia and the odds ratios for postoperative delirium, the relation of early postoperative cognitive recovery and postoperative delirium rate. A subgroup analysis will be used to categorize patients according to demographic variables relevant to the risk of postoperative delirium (age, sex, body weight) and to the preoperative score index for delirium.

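### The trial is sized for non-inferiority against a 3-point margin, but the only between-group test planned for use is Dunnett's test of zero difference, which uses no margin

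*Protocol article*

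**What the plan says.** All the main statements are in the Sample Size section, under Statistical Analysis, in the protocol article.

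- **Objective:** "This trial has the objective to evaluate if propofol + fentanyl, as well as sevoflurane + fentanyl, is non inferior to desflurane + fentanyl", judged on PD. The section adds "To test for non inferiority two comparisons are planned": propofol against desflurane and sevoflurane against desflurane.
- **Margin:** the trial is powered "to detect a non-inferiority margin difference between the group percentage of 3% in the primary end-point variable (PD rate"). The reference rate is 10%, the rate under the null of inferiority is 13%, and power is computed at a true rate of 7%.
- **Test behind the sample size:** "The statistical test used was the one-sided Score test (Farrington & Manning"), at 0.05 and 80% power, giving 275 per group and 825 in total, with no correction for multiple comparisons.
- **Test for the analysis:** "Dunnett's test will be used after ANOVA to test the null hypothesis that no group has its mean significantly different" from that of the reference group.

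The endpoint is binary. The Methods text on the Nursing Delirium Scale says "A score of 2 or more on the Nu-Desc correctly identifies the presence of delirium". The abstract says the analysis will look at differences between hypnotics and at "the odds ratios for postoperative delirium". The closing paragraph of the Discussion speaks of detecting a significant difference in PD rate.

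**The concern.** Two null hypotheses stand in one section. The sizing uses a null of inferiority by 3 points on a risk difference. The analysis sentence uses a null of equal means. Only one of them can govern the primary comparison, and only the first matches the objective.

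The score test is reported in the past tense, between the power assumptions and the software, so it describes the calculation. Dunnett's test is the one the article commits to for the future. It is also a method for means of continuous outcomes, whereas PD is yes or no.

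If the analysis followed the text as written, a non-significant result would leave open whether the margin had been exceeded. A significant result would show a difference from zero without placing it relative to 3 points. The stated power would not describe the test carried out.

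**Working it through.** **Inputs, all from the Sample Size section:** reference rate 0.10; true test-arm rate 0.07; margin +0.03; one-sided alpha 0.05; power 0.80; n = 275 per arm.

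**1. Reproduce the sample size (Farrington-Manning).** With the difference restricted to +0.03, the maximum-likelihood rates are 0.1045 (test) and 0.0745 (reference).

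- Null SD: s0 = √(0.1045×0.8955 + 0.0745×0.9255) = √0.1626 = 0.4032
- Alternative SD: s1 = √(0.07×0.93 + 0.10×0.90) = √0.1551 = 0.3938
- Distance from the margin: 0.03 − (0.07 − 0.10) = 0.06
- n = [(1.645×0.4032 + 0.842×0.3938)/0.06]² = 274.9, so 275 per arm
- Power at 275 = Φ[(0.06×√275 − 1.645×0.4032)/0.3938] = Φ(0.842) = 80.0%

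The stated figure reproduces for this test at one-sided 0.05. At one-sided 0.025 the same formula gives 350. An exact binomial calculation at 275 per arm and one-sided 0.05 gives a 4.96% chance of a non-inferiority claim at 13% against 10%, and 80.9% at 7% against 10%.

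**2. What Dunnett's test does with the same data.** The article gives no sidedness or level for it. I assume two-sided 5%, for which the critical value is 2.21 (two comparisons with one reference). The pooled ANOVA variance is computed on the 0/1 outcome.

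Case with both test arms at 13% and desflurane at 10%:

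- Mean square error ≈ (0.0900 + 0.1131 + 0.1131)/3 = 0.1054
- Standard error = √(2×0.1054/275) = 0.0277
- Threshold for significance = 2.21×0.0277 = 0.0612, about 6.1 points, or twice the margin
- True SE of the difference = √[(0.0900 + 0.1131)/275] = 0.0272
- P(non-significant) ≈ Φ[(0.0612 − 0.03)/0.0272] − Φ[(−0.0612 − 0.03)/0.0272] ≈ 0.874

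Simulation (400,000 trials per scenario, 275 per arm) agrees. The ranges cover the other test arm being at 10% or at the same rate as the arm tested.

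| True rate, test arm vs desflurane | Dunnett non-significant | Dunnett significant | Farrington-Manning declares non-inferiority (exact) |
|---|---|---|---|
| 13% vs 10% (at the margin) | 85-87% | 13-15% | 5.0% |
| 16% vs 10% (twice the margin) | 51-57% | 43-49% | 0.4% |
| 7% vs 10% (planned case) | 81-84% | 16-19% | 80.9% |

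Requiring a significant ANOVA first raises the 85-87% to 87-90%. A one-sided 5% Dunnett test for a worse result would be non-significant in 78-80% of trials at the margin.

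**3. Cost of adjusting for two comparisons.** Using the power formula of step 1 at 275 per arm:

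- One-sided 0.025 (Bonferroni): Φ[(0.06×√275 − 1.960×0.4032)/0.3938] = Φ(0.520) = 69.8%; 80% power needs 350 per arm, 1,050 in total
- One-sided 0.027 (about the Dunnett-type level): Φ(0.554) = 71.0%; 80% power needs about 341 per arm

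**The case against.** The strongest reply is that the Dunnett sentence names no endpoint and speaks of a mean, while PD is described throughout as a rate or percentage. The article has score outcomes for which ANOVA would be natural (the orientation-memory-concentration test and the Rancho Los Amigos Scale). The margin-based hypothesis is also fully specified a few lines earlier, and this is a condensed article whose full protocol and analysis plan are not shown.

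Part of this stands. The text does not prove that PD was meant, and a missing confidence-bound rule alone would be no finding. But the sentence comes directly after the PD comparisons, uses the same term for the reference group and fits their two-against-one structure. The Sample Size section mentions no cognitive endpoint. PD is therefore the natural reading, and the point rests on a stated rule that conflicts with the objective.

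Three stronger readings are tempting but unsupported:

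- **That a null result will be reported as non-inferiority.** Nothing in the article says so. The 87% figure is the error rate of a decision rule supplied here for illustration. Likewise, the 16-19% is power to show a difference, for which the article never claims 80%.
- **That the odds ratio is a third, conflicting scale.** The abstract lists odds ratios among the things to be examined. It does not make them the non-inferiority measure, and reporting them beside a risk difference is no contradiction.
- **That the sample size is wrong.** On its own inputs it is right.

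**Conclusion.** The point holds as a mismatch between the test that sized the trial and the only between-group test planned for its analysis. Dunnett's test of zero difference cannot establish non-inferiority at any result, because the 3-point margin does not enter it. The 275 per arm and 80% power are correct for the Farrington-Manning test at one-sided 0.05, and for that test only.

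The illustrative size is a pass rate of about 87% instead of 5% for an arm truly at the margin. It assumes a two-sided 5% level, both test arms at 13%, and a non-significant result being taken as non-inferiority. The conclusion about the mismatch does not depend on those assumptions. It depends only on reading the Dunnett sentence as covering PD, which its position supports but its wording does not settle. Because this concerns the primary hypothesis, it should be resolved before the data are analysed.

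**What to change.** Replace the ANOVA/Dunnett sentence, for the primary endpoint, with a statement along these lines:

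*For each of the two comparisons, the risk difference in PD (test arm minus desflurane) will be tested against +3 percentage points with the one-sided Farrington-Manning score test at 0.05. Non-inferiority is declared if the matching upper confidence bound lies below 3 points.*

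Then state that ANOVA with Dunnett's test applies only to the continuous cognitive scores. Odds ratios for PD can be reported as description.

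**Cost:** one paragraph. At one-sided 0.05 per comparison, 275 per arm and 80% power are unchanged.

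**Multiplicity is a separate decision with a price.** At 0.05 each, the chance of at least one false non-inferiority claim is bounded by 2×0.05 = 10%. If the sponsor adjusts (one-sided about 0.025-0.027), the power at 275 per arm should be restated as about 70-71%. Restoring 80% would take roughly 341-350 per arm. Either choice should be written down.
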